|                           | 2b | WHO Trial Registration Data Set 
 
Primary Registry and Trial Identifying Number:
ClinicalTrials.gov, NCT06501729.
 
Date of Registration in Primary Registry:
[Insert registration date]
 
Secondary Identifying Numbers:
Not applicable.
 
Source(s) of Monetary or Material Support:
Universidad Católica de Santiago de Guayaquil.
 
Primary Sponsor:
Universidad Católica de Santiago de Guayaquil.
 
Contact for Public Queries:
Name: [name] [name]
Email: [Insert email]
Phone: [Insert phone number]
 
Contact for Scientific Queries:
Same as above.
 
Public Title:
Potential Protective Effect of Kissing on Salivary pH Recovery After Acidic Beverage Consumption.
 
Scientific Title:
Potential Protective Effect of Buccal Kissing Between Two People on the Reduction of Salivary pH.
 
Countries of Recruitment:
Ecuador.
 
Health Condition(s) or Problem(s) Studied:
Salivary pH restoration, prevention of dental caries.
 
Intervention(s): 
 
Experimental group: Kissing intervention after acidic beverage consumption.
 
Control group: No kissing after acidic beverage consumption.
 
 
 
Key Inclusion and Exclusion Criteria: 
 
Inclusion: Participants aged 18-28, good oral health, availability of a partner.
 
Exclusion: Systemic diseases affecting salivary pH, medications altering salivary pH, severe oral pathologies.
 
 
 
Study Type:
Interventional.
 
Date of First Enrollment:
march 2025
 
Target Sample Size:
45 couples (15 per group).
 
Recruitment Status:
Not yet recruiting
 
 |

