|               |     | 
 
○ Anticholinergics: e.g., atropine.
 
 
3. Presence of oral abscesses or other severe dental conditions.
 
Justification:
These criteria were selected to minimize confounding factors that could alter salivary pH, such as systemic diseases, abscesses, or the influence of medications. The age range of 18 to 28 years was chosen to reduce the likelihood of undiagnosed chronic systemic diseases, as no specific tests will be conducted to confirm their absence; participant responses will be accepted as valid. Additionally, requiring participants to already have a romantic partner ensures that the study is conducted ethically and avoids potential discomfort from pairing participants with strangers.
 
Sociodemographic Characteristics:
Participants must reside in Guayaquil, specifically near the Universidad Católica de Santiago de Guayaquil, to facilitate travel and ensure availability for multiple appointments.
 
Sample Size:
The study aims to recruit a minimum of 15 couples per group, accounting for potential dropouts. This number was determined based on a sampling of means and a reference from a similar study.
 
Selection Process:
The recruitment process will involve an open call via social media platforms targeting university students, although being a student is not an inclusion criterion. Flyers with a QR code and a registration link will direct interested individuals to a Google Form where they will provide initial data. Eligible participants will be contacted to schedule an oral health assessment and complete a health questionnaire to confirm compliance with the inclusion criteria.
                     |

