| Sample size          | 14 | 
The sample size calculation was conducted using the G*Power statistical software (version 3.1.9.7, Fran Faul, Universität Kiel, Germany). The calculation was based on data obtained from the pilot study titled "Comparison of Salivary pH Changes after Consumption of Two Sweetened Malaysian Local Drinks among Individuals with Low Caries Experience: A Pilot Study". This study measured salivary pH changes after consuming acidic beverages and provided the necessary statistical parameters for sample size estimation.
 
Specifically, the following values from the pilot study were used:
 
 
Control group (mineral water): mean = 7.10, SD = 0.18.
 
Experimental group (local drink): mean = 6.86, SD = 0.18.
 
 
To calculate the effect size (<math>f</math>) for ANOVA, the means and standard deviations were combined using the formula:
 $n = \frac{(2 * (Z\beta + Z\alpha)^2 * \sigma^2)}{\Delta^2}$ 
Given the mean difference (7.10 - 6.86 = 0.24) and pooled SD of 0.18, <math>d=1.33d=1.33d=1.33</math>. Dividing by the square root of the number of groups (<math>k=3</math>), the resulting effect size was <math>f=0.76</math>, which is considered a large effect size.
 
The following input parameters were used in G*Power:
 
 
Effect size (<math>f</math>): 0.76 (large effect size based on observed data).
 
Alpha error probability (<math>\alpha</math>): 0.05.
 
Power (1-<math>\beta</math>): 0.95.
 
Number of groups: 3.
 
 
The output indicated that a total sample size of 30 participants is required to achieve a power of 95%, with 10 participants per group. To account for potential dropouts, an additional 20% will be recruited, resulting in a total of 36 participants (12 per group).
 
This effect size and resulting sample size are justified based on the observed differences in the pilot study, which measured salivary pH using similar methods (pH meter, unstimulated saliva samples in test tubes) and reported statistically significant differences between groups. Using this approach ensures that the sample size is both statistically adequate and logistically feasible for this study.
 |

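### The protocol sets two conflicting sample sizes, 36 participants (12 per group) and 45 couples (15 per group), and does not show the dropout allowance claimed for the second

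*Protocol*

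**What the plan says.** Three places in the protocol fix the sample size.

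- **Item 14 (Sample size)** gives a one-way ANOVA calculation with three groups, alpha 0.05, 95% power and an effect size f of "0.76 (large effect size based on observed data". Its result is 30 in total, which "is required to achieve a power of 95%, with 10 participants per group". It then recruits a further 20% and ends at "36 participants (12 per group".
- **Item 2b (registration data set, target sample size)** gives "45 couples (15 per group".
- **Item 10 (Eligibility criteria, Sample Size)** gives a minimum of 15 couples per group, "accounting for potential dropouts. This number was determined based on a sampling of means" and a similar study. It shows no dropout rate, inputs or calculation.

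Item 16c (Implementation) gives the randomisation code to each pair, not to each person.

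**The concern.** All three statements are current text, and none refers to or overrides another. A reader cannot tell whether recruitment ends at 36 or 45, or whether the count is of persons or couples. Because the couple is the coded unit, 36 participants has two readings that differ by a factor of two.

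The dropout allowance matters here because losses reduce the analysed number directly. Items 11b and 18b remove the data of those who withdraw, and item 20b makes the primary analysis complete-case. A target that is said to allow for dropout should therefore show the allowance.

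**Working it through.** **Inputs (item 14).** f = 0.76; alpha = 0.05; power = 0.95; k = 3 equal groups; mean difference 0.24 and SD 0.18 ("Given the mean difference (7.10 - 6.86 = 0.24) and pooled SD of 0.18"). The 20% loss used in steps 3 and 4 is an assumption: the protocol states a 20% addition, not an expected loss rate.

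**1. Reproduce item 14.** Power of the one-way ANOVA F test comes from the noncentral F distribution with df = 2 and N − 3 and noncentrality λ = f²N.
- N = 30: λ = 0.76² × 30 = 17.33, power 95.0%.
- N = 27 (9 per group): λ = 15.60, power 92.3%.

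So 10 per group is the smallest equal-group size that reaches 95%, and the stated 30 reproduces. The stated final number also reproduces: 30 × 1.2 = 36.

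**2. Set the totals in each unit.**

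| Statement | Couples | Persons |
|---|---|---|
| Item 14, if one analysed member per couple is counted | 36 | 72 attending |
| Item 14, if persons are counted | 18 (6 per group) | 36 |
| Items 2b and 10 | 45 | 90 attending |

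No reading of item 14 gives 45 couples.

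**3. Power at the protocol's own f = 0.76, one analysed member per couple.**

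| Start | Loss | Analysed N | λ = 0.76²N | Power |
|---|---|---|---|---|
| 36 | 20% (assumed) | 28.8, about 29 | 16.75 | 94.2% |
| 45 | 20% (assumed) | 36 | 20.79 | 98.0% |
| 18 | none | 18 | 10.40 | 74.3% |

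**4. What 36 covers.** 1 − 30/36 = 16.7%. A 20% loss leaves 36 × 0.8 = 28.8, just under 30. To keep 30 after a 20% loss takes 30/0.8 = 37.5, or 10/0.8 = 12.5 per group, rounded up to 13 per group and 39 in total.

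**5. Where 15 per group could come from.** Item 14 prints the two-means formula n = 2(Zβ + Zα)²σ²/Δ². With two-sided alpha 0.05 and 95% power:

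n = 2 × (1.645 + 1.960)² × 0.18² / 0.24² = 14.6, so 15 per group, with no dropout allowance.

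Other settings give other values: 13 per group one-sided at 95% power, and 12 at 90% or 9 at 80% power (both two-sided).

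**The case against.** **Item 14 does what it says.** It promises to recruit an additional 20%, and 30 × 1.2 = 36 is exactly that. It does not say that 20% are expected to drop out. A reader might infer that 36 lacks the allowance it claims, but the text does not support this. What stands is minor: 36 covers a 16.7% loss, and even a 20% loss leaves about 94% power at the stated f.

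**Item 10 names no rate, so there is no stated rate for 15 per group to miss.** Against the only stated requirement, 10 per group, 15 would absorb a loss of one third (1 − 30/45). The match with the uninflated 14.6 is suggestive, and fits item 10's mention of a sampling of means, but it depends on the settings chosen. At 90% or 80% power the formula gives 12 or 9, and 15 would then include an allowance. A reader might conclude that the dropout claim is false; the protocol supports only that the allowance is not shown.

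**The conflict costs little power if both totals count one analysed member per couple.** This is right: about 4 percentage points at the protocol's f. Larger gaps can be produced with smaller effect sizes, but those rest on a separate question, whether f was correctly derived from the mean difference, and are not the size of this inconsistency.

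None of these objections reconciles 36 participants with 45 couples.

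**Conclusion.** The conflict in number and unit is certain and needs correction, because the recruitment target has no single value. Its size depends on the unit. With one analysed member per couple and an assumed 20% loss, power is about 94% from 36 and 98% from 45. If 36 participants means 18 couples with one analysed member each, power is about 74% before any loss. These figures take the protocol's f = 0.76 and the one-way ANOVA as given.

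The dropout allowance claimed in item 10 is not shown, which is a gap in the derivation and not proof of an error. The 20% addition in item 14 is carried out as worded; only its coverage, 16.7% and not 20%, deserves clarification.

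**What to change.** State one sample size in one unit in items 2b, 10 and 14. Couples is the natural unit, since the pair carries the randomisation code. Add the number of analysed members per couple, which needs an explicit decision because both partners drink in experimental group 2.

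Keeping the 45 couples already stated is the simplest choice. Item 14 should then give the assumed dropout rate and the evaluable number and power that follow. For example, a 20% loss leaves 12 couples per group, with about 98% power at f = 0.76 and one analysed member per couple, subject to any separate correction of f. If 20% is meant as an expected loss, divide the required number by 0.8 in place of multiplying by 1.2.

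In item 10, either show the rate and calculation behind the allowance or drop that wording.

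The cost is wording in three places, with no enrolment beyond the figure in items 2b and 10. Item 2b lists recruitment as not yet started, so on that status the correction can be made before enrolment.

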| Study setting                                             | 9  | 
The study will be conducted at the dental clinics of the Universidad Católica de Santiago de Guayaquil. These facilities provide a controlled and sanitized environment, adhering to strict biosecurity protocols. Data collection will take place two days per week, during which the space will be reserved exclusively for the study.
 
The following arrangements have been made to ensure participant comfort and privacy:
 
 
○ Oral Health Assessments: Dental chairs within the clinic will be used to evaluate the oral health of participants prior to the intervention.
 
○ Privacy During Interventions: Private spaces separated by screens (biombos) will be set up to allow participants to kiss in a comfortable and discreet environment.
 
○ Saliva Sample Collection: Saliva samples will be collected and pH measurements will be performed in the same private setting immediately following the intervention.
 
 
This controlled environment is designed to ensure participant safety, facilitate standardized data collection, and maintain the integrity of the study.
 |
| Eligibility criteria                                      | 10 | 
Inclusion Criteria:
 
Participants must meet the following criteria to be eligible for the study:
 
 
1. Be between 18 and 28 years old.
 
2. Have good oral health, defined as a CPO index <math>\leq 3</math>, according to the criteria of the World Health Organization.
 
3. Be in a romantic relationship with a partner willing to participate in the study.
 
4. Have sufficient availability to attend all study appointments.
 
 
Exclusion Criteria:
 
Participants will be excluded from the study if they meet any of the following conditions:
 
 
1. Presence of systemic diseases that could alter salivary pH (e.g., diabetes, autoimmune disorders).
 
2. Use of medications that may affect salivary pH, including: 
 
○ Antidepressants (tricyclics): e.g., amitriptyline.
 
○ Antihistamines: e.g., diphenhydramine.
 
○ Beta blockers: e.g., propranolol.
 
○ Diuretics: e.g., hydrochlorothiazide.
 
 
 
     |

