| Interventions | 11a | 
Experimental Groups (Intervention):
Participants in the experimental groups will engage in a French kiss, defined as a passionate kiss involving the exchange of salivary fluids through the mutual introduction of tongues into each other's mouths, along with lip contact. Participants will receive instructions to perform this kiss for a duration of 40 seconds. While this duration is arbitrary and will be acknowledged as a limitation in the protocol, no prior studies provide a guideline for the specific duration of this type of kiss.
 
 
○ Setting: The intervention will take place in a private space within the dental clinic of the Universidad Católica de Santiago de Guayaquil. Each cubicle, equipped with a dental chair, will be enclosed with screens to ensure the privacy of participants. After completing the kiss, participants will leave the cubicle to provide an unstimulated saliva sample, which will be analyzed to measure pH.
 
 
Control Group:
Participants in the control group will not kiss but will still be required to bring their partners to ensure comparable conditions. The individual who consumes the acidic beverage will remain in the same cubicle for 40 minutes, providing unstimulated saliva samples every 5 minutes, as is required for the experimental groups. The control participants will remain seated and follow the same sample collection timeline as the intervention groups.
 
Implementation Standards:
 
 
○ The intervention (kissing) will be self-administered by participants. The research team will observe the initiation of the kiss to ensure it begins appropriately and will then start the timer
 
 |

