|  | 11c | 
Strategies to improve adherence to intervention protocols, and any procedures for monitoring adherence.
To verify adherence, one of the investigators will observe the initiation of the kiss to ensure proper compliance and will start the timer for the specified 40 seconds. The investigator will notify the participants when the time is complete.
No further direct supervision will be performed during the kiss to respect the privacy of the participants.
                                                                                                                                                                                                                                                                                                                                                                                                                                                                                                                                                                                                                                                                                                                                                                                                                                                                                                                                                                                                                                                                                                                                                                                                                                                                                                                                                                                                                                                                                                                                                                                                                                                                                                                                                                                                                                                                                                                                                                                                                                                                                                                                                |

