| Implementation                              | 16c | 
Implementation:
During enrollment, each participant pair will receive a unique code. These codes will be sent to [name], who will perform the randomization without access to any identifying information, ensuring impartiality. She will then relay the group assignments back to the study coordinator, who will oversee the implementation during the intervention phase. This process maintains the integrity of the randomization and minimizes potential biases.
                                                                                                                                                                                                                                                                                                                                                                                                                                                                                                                           |
| Blinding (masking)                          | 17a | 
Who Will Be Blinded:
This study will incorporate blinding at three levels to minimize bias and ensure the integrity of the results:
 
 
1. Participants: Participants will remain unaware of their group assignment (control or experimental) until the day of the experiment. This approach prevents anticipatory salivation or behavioral changes that could influence the results.
 
2. Investigators: The research team responsible for collecting and analyzing the data will not know the group assignments during the intervention phase. The assignments will only be revealed after data collection is complete to avoid any unintentional biases.
 
3. External Randomizer ([name]): [name], who performs the randomization process in Miami, USA, will be blinded to participant identities. She will only receive anonymized participant codes for allocation, ensuring impartiality in group assignments.
 
 |

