|                                                           |     | 
information will only be disclosed on the day of the intervention to maintain blinding.
 
 
○ Investigators: The assignment of participant codes to groups will be conducted by [name] using the RANDOM.ORG platform. The research team will only receive group assignments linked to participant codes after all data has been collected.
 
○ External Randomizer: [name] will not have access to any identifying information about participants. She will receive only the anonymized codes, ensuring she remains blinded to the participants' identities.
 
                                                                                                                                                                                                                                                                                                                                                                                                                                                                                                                                                                                                                                                                                                                                                                                                                                                                    |

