| Data collection methods                                   | 18a | 
The primary outcome of this study is the time required for salivary pH to return to neutral (pH 7.0) after the kissing intervention, compared to the control group. Baseline data, including the initial pH of unstimulated saliva before the intervention, will also be collected. Secondary outcomes include salivary pH measurements at defined time intervals (e.g., immediately after the intervention and every 5 minutes up to 40 minutes).
 
Data Collection Process:
 
 
○ Participants will expectorate saliva into sterile 3 mL conical Eppendorf tubes at each designated time point.
 
○ A calibrated pH meter will be used to measure the pH of the collected saliva. Calibration will be performed using standard buffer solutions at pH 4.01 and pH 7.01 before each data collection session, ensuring accuracy and reliability of the measurements.
 
○ All pH measurements will be conducted by trained members of the research team, who will follow a standardized protocol to minimize variability and ensure data quality. Duplicate measurements will be taken for 10% of the samples to verify consistency.
 
 
Data Recording:
 
 
○ Measured values will be entered directly into a secure, cloud-based Excel spreadsheet accessible only to authorized members of the research team. This ensures data integrity and confidentiality.
 
 |

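### Items 17a/17b say the data-collecting team is blind until collection ends, but items 9, 11a, 11c, 16c and 18a reveal the group and describe no separation of roles

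*Protocol*

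**What the plan says.** The blinding claim is in items 17a and 17b of the protocol. Item 17a says of the investigators: "The research team responsible for collecting and analyzing the data will not know the group assignments during the intervention phase". It adds: "The assignments will only be revealed after data collection is complete to avoid any unintentional biases". Item 17b gives the mechanism: "The research team will only receive group assignments linked to participant codes after all data has been collected".

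The procedures are in other items:

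- Item 11a, implementation standards: "The research team will observe the initiation of the kiss to ensure it begins appropriately and will then start the timer". Item 11c narrows this to a single person: "one of the investigators will observe the initiation of the kiss to ensure proper compliance and will start the timer".
- Item 16c: the randomizer returns the assignments to the study coordinator, who oversees the intervention phase.
- Item 18a: "All pH measurements will be conducted by trained members of the research team".
- Item 9: "Saliva samples will be collected and pH measurements will be performed in the same private setting immediately following the intervention".
- Item 11a, setting and control group: kissing couples leave the cubicle to give their sample, whereas the control participant who drank stays in the cubicle for the 40 minutes.

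Participants are to learn their group on the day of the session (17a, 17b). The reason given is to avoid anticipatory salivation.

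**The concern.** Kiss versus no kiss cannot be hidden from anyone who sees the kiss begin. Withholding the list of codes and groups does nothing for that person. If the people who watch the kiss may also collect samples, read the meter or enter values, the trial would be reported as having blinded data collection that its procedures do not secure.

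The primary outcome makes this worth settling. It is the time until pH is back at about 7 (item 12; 7.0 in item 18a), read off samples 5 minutes apart. Someone who knows the group could influence how a sample is handled, whether a reading is repeated, or whether a value near the threshold counts as recovered.

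A smaller, related point concerns participants. Item 12 takes a baseline sample and a post-beverage sample before the kiss. No item says at what moment of the day couples are told their group, so nothing ensures that these two samples come before disclosure.

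**Working it through.** No arithmetic decides this point. The check sets the claim beside each procedure and asks what the procedure reveals, and to whom.

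1. **Scope of the claim.** Item 17a covers everyone who collects or analyses data, for the whole intervention phase. Item 17b supports it with one measure only: the list is kept back.

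2. **Watching and timing (11a, 11c).** The observer sees a kiss start and knows at once that the couple is not in the control group. Item 11a says that researchers then withdraw for privacy, but the start is enough.

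3. **Coordinator (16c).** This person holds all three group labels during the intervention phase. If the coordinator belongs to the research team, this contradicts 17b directly. If not, 17 should say so.

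4. **pH reading (18a, 9).** The readers are research-team members, the term that 11a also uses for those who watch the kiss. Item 9 puts sampling and reading in the private setting of the intervention. No item assigns the two tasks to different people.

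5. **Movement (11a).** Kissers come out to give the sample and the control drinker stays in. A staff member who saw no kiss can still tell kiss from no kiss. This cue cannot separate experimental group 1 from group 2. It also does not fit item 9, which keeps sampling and measurement in the private setting, so the two items must be reconciled.

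6. **Samples exposed.** Item 12 gives 1 baseline sample, 1 post-beverage sample and 9 post-intervention samples, so 1 + 1 + 9 = 11 per participant. All 9 post-intervention samples are taken after the group has become visible to the observer.

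7. **Safeguards that remain.** The outcome is a meter reading (12), with calibration before each session (18a). Samples are labelled and timestamped against the 5-minute schedule (11c). Tubes carry a code only (Appendix 2, section 3). These limit what a knowing reader can change.

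8. **Disclosure to participants.** Telling couples kiss or no kiss only after the post-beverage sample would keep the baseline sample free of that knowledge in every group. It would not fully do so for the post-beverage sample. Both partners drink in experimental group 2 (8), while the control text refers to one drinker (11a), and couples are told the study procedures in advance (17b). A couple in which both drink may therefore guess that they will kiss.

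**The case against.** The strongest reply is that the protocol nowhere says that one person both times the kiss and reads the pH. Item 17a is limited to those who collect and analyse data, 11c gives the watching to one investigator, and 16c gives the assignments to one coordinator. The pages between items 4 and 5c are not in the copy at hand and may assign roles. This stands as a limit on the point. A reader might infer that the trial is open-label throughout collection, reading and entry; the text does not go that far. What it supports is that no separation is described and that the wording of 17 conflicts with that of 11a, 11c and 16c.

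A second reply is that an instrument reading on timestamped, coded samples leaves little room for bias. This is largely right and bears on size. It does not make the blinding statement true.

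Two further inferences should be resisted. One is to size the bias from the mean and SD in item 14. Those are values from the drinks arms of an outside pilot study and do not describe pH during recovery in this trial. The other is that staff may choose between duplicate readings. Item 18a takes duplicates on 10% of samples to check consistency and describes no such choice.

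Nor do the documents say that couples are told before the baseline sample, only that they are told that day. Item 17a openly limits participant blinding to the period before it, so this is a gap in timing and not part of the contradiction.

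**Conclusion.** The point holds as an internal contradiction. Items 17a and 17b claim that the data-collecting team stays blind until collection is complete, and items 9, 11a, 11c, 16c and 18a describe a trial in which that is not secured. The conclusion rests on the wording alone and on one assumption: that a person who sees the kiss start knows that the couple is not in the control group. It does not depend on the same individual doing both tasks.

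Any resulting bias is limited by the instrument reading, the codes and the timestamps, and the documents give no basis for a figure. Blinding of the analyst is still achievable. The protocol should be corrected before the first session, because the procedures can be changed only until then.

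**What to change.** - **Restate 17a and 17b.** Declare participants, the coordinator and the person who supervises the kiss unblinded from the intervention onward.
- **Separate the reading.** Have the coded tubes read promptly, out of sight of the cubicles, by an existing team member who did not supervise that couple. If this cannot be arranged, withdraw the claim of blinded outcome measurement.
- **Use one sampling place for all groups,** and reconcile items 9 and 11a accordingly.
- **Mask the analyst** with labels A, B and C until the analysis is fixed.
- **Delay disclosure where feasible.** Tell couples kiss or no kiss only after the post-beverage sample. State that this protects the baseline sample in all groups but cannot fully mask the post-beverage sample in experimental group 2.

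The cost is a lower declared level of blinding and a small change of routine. The routine must still meet the requirement for immediate analysis in Appendix 2, section 2, so the reading place has to be close by. It also needs at least two team members per session; the protocol speaks of trained members in the plural but does not give the team's size.
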